
### Data monitoring

This CRCT will be completed before the other clinics elsewhere in Palestine have completed their national implementation. PHC serving as controls for this CRCT will implement the eRegistry at the earliest opportunity that capacity allows. As there is insufficient manpower and infrastructure to introduce the intervention to all control sites earlier in case of overwhelming effectiveness, and no power of the research results to reverse the national decision to implement the eRegistry earlier than planned, no data monitoring committee will be established. Data management and monitoring will be performed in accordance with the SOP of the Palestinian maternal and child health eRegistry for routine registry operations [26].

### Harms

While the national implementation of the eRegistry in Palestine may create unexpected stress to the health system, in particular during the implementation and transition period, the study has no risks in itself. This CRCT only utilizes the moment of opportunity of an ongoing implementation to study a new health systems approach. Whether the eRegistry brings benefits or harms to the health system, the effect of the study itself is a measure of fairness since the sites receiving the new system first are chosen randomly within the districts.

### Audit and monitoring

CRCT monitoring is organized by CISMAC and will be independent of the researchers and sponsors. The first monitoring visit to assess CRCT readiness to begin recruitment took place on 28 and 29 September 2016. The second monitoring visit, during the trial, is expected within the first 6 months of inclusion.

### Confidentiality

Data confidentiality will be handled in accordance with the Palestinian MoH legal framework for maternal and child health electronic registries. This CRCT will only utilize anonymous registry data to enable the assessment of effectiveness, and only data that is pertaining to the outcome measures reflecting ANC provision. We will publish only aggregate data. We will not publish any data on individual clients, care providers, or identifiable clusters.

### Access to data

The data in the eRegistry belong to the Palestinian MoH and at no point or circumstance will the researchers have access to the entire registry or identifiable data of any kind.

### Dissemination plan

We followed the Standard Protocol Items: Recommendations for Intervention trials (SPIRIT) guidelines while writing this protocol (see Additional file 4). We will publish the results of the CRCT in peer-reviewed open-access journals and in presentations at scientific meetings and congresses. We will report the results in accordance with the Consolidating Standards of Reporting Trials (CONSORT) guidelines and the mHealth Evidence Reporting and Assessment (mERA) checklist. We will acknowledge any change in the study outcomes, study design, sample sizes, or significant administrative aspects that will impact the study’s nature when disseminating the findings. All authorship will be decided based on the recommendations of International Committee of Medical Journal editors. We will report the research findings to the Palestinian MoH directly. Summaries of the results and other relevant information will be published on the eRegistries website [23].

## Discussion

Electronic health information systems and programs are frequently tested in isolation, often as pilots or with less robust study designs [31]. This CRCT aims to contribute to filling this evidence gap. In order to study effectiveness of the intervention in the health system, we have designed a pragmatic CRCT. We have worked closely with the Palestinian MoH to plan the intervention and the timelines for the implementation of the eRegistry. All our communication strategies to the study clinics have always been through the Palestinian MoH via established channels within the health system in an attempt to keep monitoring of sites robust but as close to real-world settings as possible. We have striven to maintain generalizability of study findings by including a large representative sample of PHC and having no individual-level eligibility criteria. Data for outcome measures are derived from existing data collection pathways for the eRegistry in Palestine. The design and implementation of this CRCT places emphasis on the outcomes, as well as the feasibility of their measurement, in registry settings within the health system. Loss to follow-up is expected to be minimal since all our data sources are part of the eRegistry. We have designed outcome measures to directly reflect the effect of the intervention within the setting of an electronic registry, justifying the use of secondary data, where the process outcomes are based on the care providers’ own documentation of process, and health outcome measures are based on data collected independently from the care provider.

There are some limitations to the design of the CRCT. Pregnant women from intervention and control PHC are referred to the same high-risk clinics, where care providers use both paper records (for women referred from control PHC) and the eRegistry (for women referred from intervention PHC). This may lead to some contamination, which may underestimate the true effect of the intervention. About 5–10% of care providers in the study clinics work both in intervention and control PHC. This is another source of contamination that may potentially lead to effectiveness underestimation. Since the data for process outcomes is dependent on completeness of documentation by the care provider, there might be missing or incomplete data to inform some of the outcome indicators. We recognize that PHC location, activities, and staff are vulnerable to changes in public health planning and policy. We have tried to mitigate the risk of this affecting the study design by working closely with the Palestinian MoH and maintaining strong stakeholder involvement.

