
### Objectives

#### Primary objectives

To estimate the effectiveness of the eRegistry’s interactive checklists and clinical decision support on: 1) improving the provision of timely and appropriate screening and management for important conditions during ANC; and 2) health outcomes for the mothers and the newborns.

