### Intervention

Care providers in the intervention PHC have received the eRegistry’s interactive checklists with clinical decision support. During the first 3–6 months, all intervention PHC had both paper and electronic files, as only new enrollments of pregnancies are included in the eRegistry. Care providers in the control PHC will continue using the current system of paper-based files throughout the trial period. In terms of the national implementation, the control PHC will receive the eRegistry at a later stage than the intervention PHC.

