#### Intervention tool

The intervention tool is the eRegistry’s interactive checklists and clinical decision support for ANC (Table 1). The interactive checklists and the current paper-based files include the same items and data points. The eRegistry allows for seamless incorporation of clinical workflow and guideline support in addition to reminders of daily clinical procedures and referrals (Table 1). All intervention PHC have been provided with desktop computers to be used by care providers in the consultation rooms. Care providers enter data on pregnant women into the eRegistry at the point-of-care (Table 1), and this data entry triggers the guideline-based decision support system (Figs. 2, 3 and 4). Each user has a unique username and password identifying their authorized access to the eRegistry in Palestine, with functionalities defined by their roles. The eRegistry is accessed by care providers using a Google Chrome browser. The full extent of the intervention is available at the demonstration eRegistry website which can be accessed through the link provided in reference [25].

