#### Adherence

The eRegistry will fully replace the paper-based system. It is mandatory for use by care providers in the public health system in the intervention areas. Care providers in the intervention PHC have been trained on how to contact support staff in case of any problems with the software or infrastructure. Standard operating procedures (SOP) of the eRegistry in Palestine include routines for replacing malfunctioning computers and providing a back-up wireless internet solution within 24 h in case of internet disruption. The SOP also include measures for routine monitoring of use of the eRegistry and periodic data quality checks [26].

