### Outcomes

The focus of the outcome measures have been informed by national stakeholder consultations as representing key areas of quality concern in the Palestinian context, and to serve as sentinel outcomes for the overall quality of care. The adverse pregnancy outcomes reflect conditions that put the baby and/or mother at risk during labor or after delivery, and that could or should have been identified and/or managed prior to labor and delivery. The process (adherence) outcomes (Table 2) for the screening and management of the risk conditions and the corresponding adverse pregnancy outcomes (Table 3) will be assessed as primary outcomes. We have defined indicators to measure the process (adherence) outcomes (Additional file 1) based on the current guideline-based algorithms for management of conditions during ANC in Palestine (Additional file 2). Secondary outcomes are given in Table 4.

**Table 2 Tab2:** Primary process (adherence) outcomes, source of data, measurement sequence, and definitions

Process (adherence) outcomes	Source of data	Measurement sequence	Definitions
Timely and appropriate screening and management of anemia during pregnancy	Case records data from the PHC in the eRegistry	Registrations continuously at point of care, data export to the trial monthly	Proportion of women attending ANC who receive: 1. anemia screening at booking, and 2. screening at any ANC visits at 24 and 36 weeks if no anemia detected, and 3. rescreening after 1 month if mild or moderate anemia is detected, and 4. referred to high-risk clinic if refractory mild or moderate anemia is detected, and 5. referred to hospital if severe anemia is detected.
Timely and appropriate screening and management of hypertension in pregnancy	Case records data from the PHC in the eRegistry	Registrations continuously at point of care, data export to the trial monthly	Proportion of women attending ANC who receive: 1. blood pressure measurement at booking visit, and 2. blood pressure measurement at every ANC visit, and 3. appropriate laboratory tests for mild hypertension, and 4. referred to high-risk clinic hospital for chronic or gestational hypertension, and 5. referred to hospital for hypertension with proteinuria or signs of eclampsia.

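### The four primary process outcomes claim care received but measure care recorded, and the intervention replaces the record in one arm only

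*Protocol article*

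**What the plan says.** All references are to the protocol article.

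- **Objective.** Under Primary objectives, the first aim is "improving the provision of timely and appropriate screening and management for important conditions during ANC".
- **Outcome definitions.** Table 2 (Outcomes) words each process outcome as care that women get. For anemia it begins: "Proportion of women attending ANC who receive: 1. anemia screening at booking, and 2. screening at any ANC visits at 24 and 36 weeks". The steps are joined by 'and', so a woman counts only if every step that applies to her was done.
- **Source.** Table 2 names clinic case records as the only source. The Discussion confirms that "process outcomes are based on the care providers’ own documentation of process" and offers this as part of the justification for secondary data.
- **Record in the intervention arm.** Under Adherence: "The eRegistry will fully replace the paper-based system". Under Intervention tool: "Care providers enter data on pregnant women into the eRegistry at the point-of-care (Table 1), and this data entry triggers the guideline-based decision support system".
- **Record in the control arm.** Under Intervention: "Care providers in the control PHC will continue using the current system of paper-based files throughout the trial period". Under Data extraction methods, completed paper files are keyed in by registry staff after delivery.
- **Limitation as stated.** The Discussion has a sentence opening "Since the data for process outcomes is dependent on completeness of documentation by the care provider", and it concludes only that data for some indicators might be missing or incomplete.

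**The concern.** Allocation changes two things at once: the care, through checklists and decision support, and the instrument that measures the care, through the record. Data entry is also how the intervention is delivered, so a provider who uses it as intended tends to leave a fuller record. If care is given equally in both arms but written down less often on paper, the process outcomes will differ between arms with no difference in care.

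The limitations paragraph does not say this. It gives a direction, underestimation, for both sources of contamination, but none for incomplete documentation and no hint that it may differ by arm. A reader would take a positive process result as evidence of more screening and management, when the data cannot separate that from more complete recording.

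**Working it through.** **1. The plan's own figures.** Sample size gives 120 clusters, mean size 44, ICC 0.04 for process outcomes, coefficient of variation of cluster size 0.85, two-sided 5% (two-sided from Statistical methods) and control prevalence 0.40–0.60.

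- Design effect = 1 + [(0.85² + 1) × 44 − 1] × 0.04 = 3.99, as stated.
- Women per arm = 60 × 44 = 2640. Effective n = 2640 / 3.99 = 662.
- Power = Φ[(|p₂ − p₁| − 1.96 × SE₀) / SE₁], with SE₀ = √[2p̄(1 − p̄)/n] and SE₁ = √{[p₁(1 − p₁) + p₂(1 − p₂)]/n}.
- This gives 0.96 for 0.40 v 0.50 (25% relative) and 0.93 for 0.60 v 0.69 (15% relative). Read that way, the stated power above 90% is reproduced. The sample size is not in dispute.

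**2. Routine recordings each outcome needs** (Table 2, woman without the condition):

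- Hypertension and fetal growth each include a step at every visit. Palestinian context gives an average of 4.8 visits, so k = 4.8. For fetal growth this is a little generous, because fundal height is first measured at 16–20 weeks.
- Anemia: booking, 24 weeks and 36 weeks, so k = 3.
- Diabetes: booking and 24–28 weeks, so k = 2.

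**3. Spurious risk ratio when care is identical.** Let d be the relative shortfall in recording per step on paper. If omissions are independent and a blank scores as not done, RR = (1 − d)^(−k). The values of d are assumptions; the article reports none.

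| d per step | k = 4.8 | k = 3 | k = 2 |
|---|---|---|---|
| 1% | 1.05 | 1.03 | 1.02 |
| 2% | 1.10 | 1.06 | 1.04 |
| 3% | 1.16 | 1.10 | 1.06 |
| 5% | 1.28 | 1.17 | 1.11 |

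**4. Shortfall that alone produces the smallest targeted effect.** Solving d = 1 − 1.15^(−1/k) gives 2.9% (k = 4.8), 4.6% (k = 3) and 6.7% (k = 2).

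**5. Chance that a 3% shortfall is declared significant.** At recorded control prevalence 0.50 and k = 4.8, p₂ = 0.50 × 1.157 = 0.579, SE₀ = 0.0274 and SE₁ = 0.0273. The probability is Φ[(0.079 − 0.054)/0.0273], about 0.82. For k = 3 (0.50 v 0.548) it is 0.41, and for k = 2 (0.50 v 0.531) it is 0.21. Over control prevalence 0.40 to 0.60 the ranges are 0.64–0.95, 0.29–0.58 and 0.15–0.29.

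**6. What each safeguard can see.**

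- Same items in both records (Intervention tool): equalizes the fields, not how fully they are filled.
- Double extraction of about 10% of paper files (Data extraction methods): re-reads the same paper, so it checks transcription.
- Independent collectors unaware of the outcome measures, and blinded analysts (Blinding): both act after the record is made.
- Monitoring of use and periodic data quality checks (Adherence): not described as comparing the record with care given.
- Complete-case analysis with possible imputation (Statistical methods): does not remove a between-arm difference in recording.

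None of these detects care that was given but not recorded.

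**The case against.** The strongest reply has five parts.

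- **The source is disclosed.** The Discussion says openly that process data are the provider's own documentation and contrasts them with independently collected health outcomes. That is true, but disclosing the source does not disclose that its completeness may depend on the arm.
- **The safeguards are several.** A reader might infer that double extraction is the only one. It is not, as step 6 of the working shows. They reduce transcription error and biased handling of data; the gap that remains is unrecorded care.
- **The illustration rests on assumptions.** This stands. If omissions cluster within women or staff, compounding weakens. The article does not fix whether a blank scores as not done or as missing. The direction is likely, not certain: outages and back-dated entry from paper back-up, which Statistical methods anticipates, could lower electronic recording.
- **Another primary outcome is nearly independent.** Hospital staff collect the adverse pregnancy outcomes in a system not linked to the eRegistry. This limits the point to the four process outcomes, although the two components that require a condition to have gone undetected in pregnancy may draw on the antenatal record.
- **Sensitivity analyses belong in an SAP.** Fair. The SAP is not shown, and the absence of a tipping-point analysis from the article is not itself a fault. It is proposed as a remedy for what the article does state.

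A reader might also infer that the Discussion claims its measures directly show provision of care. It does not. It says they were designed to show the intervention's effect within an electronic registry. The mismatch lies between the data source and the wording of the objective and Table 2.

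**Conclusion.** The point stands for the four primary process outcomes. They are defined as care received, measured only as care recorded, and the randomized factor replaces the record. A positive process result could reflect more care, fuller recording or both, and the planned data cannot tell these apart.

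The possible size differs by outcome. Under the stated assumptions, a 3% per-step shortfall on paper reaches the targeted 15–25% range only for hypertension and fetal growth. It would be tempting to apply the risk ratio of 1.16 and the 82% chance of significance to all four outcomes. The definitions do not support that, because anemia and diabetes have no every-visit step. Nor do the documents show that recording does differ, or that a positive result would be an artifact. They show only that a small difference could matter and that nothing described would reveal it.

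**What to change.** 1. **Wording.** In Primary objectives, Table 2 and the Discussion, state the process outcomes and the conclusion drawn from them as documented screening and management. Add to the limitations that recording may differ between arms and that this may overestimate the effect.
2. **Tipping-point analysis.** For each process outcome, report the control-arm under-recording per step at which the risk ratio reaches 1, d = 1 − RR^(−1/k), and at which its 95% confidence interval first includes 1, d = 1 − L^(−1/k), where L is the lower limit. Use that outcome's own k, and state the independence assumption and how blanks are scored. This shows how little under-recording would explain the result. It cannot show whether that much occurred.

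Both changes use data already held and leave conduct untouched, which matters because recruitment has begun. The cost is a slightly more modest process conclusion and a little extra analysis.

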### Trial status

The CRCT started recruitment on 15 January 2017.

## Abbreviations

ANC: Antenatal care
CISMAC: Center for Intervention Science in Maternal and Child Health
CRCT: Cluster randomized controlled trial
DHIS2: District Health Information System 2
eHealth: Electronic health
eRegistry: Electronic registry
ICC: Intracluster correlation coefficient
mHealth: Mobile health
MoH: Ministry of Health
NGO: Nongovernmental organizations
PHC: Primary healthcare clinics
PNIPH: Palestinian National Institute of Public Health
RCT: Randomized controlled trial
RMNCH: Reproductive, maternal, newborn and child health
SOP: Standard operating procedures
